# The PerPAIN trial: a pilot randomized controlled trial of personalized treatment allocation for chronic musculoskeletal pain—a protocol

**DOI:** 10.1186/s40814-022-01199-6

**Published:** 2022-12-09

**Keywords:** Chronic pain, Treatment personalization, Precision therapy, Personalized allocation, Psychotherapy

## Abstract

**Background:**

The therapy of chronic musculoskeletal pain (CMSP) is complex and the treatment results are often insufficient despite numerous therapeutic options. While individual patients respond very well to specific interventions, other patients show no improvement. Personalized treatment assignment offers a promising approach to improve response rates; however, there are no validated cross-disease allocation algorithms available for the treatment of chronic pain in validated personalized pain interventions. This trial aims to test the feasibility and safety of a personalized pain psychotherapy allocation with three different treatment modules and estimate initial signals of efficacy and utility of such an approach compared to non-personalized allocation.

**Methods:**

This is a randomized, controlled assessor-blinded pilot trial with a multifactorial parallel arm design. CMSP patients (*n* = 105) will be randomly assigned 1:1 to personalized or non-personalized treatment based on a cluster assignment of the West Haven-Yale Multidimensional Pain Inventory (MPI). In the personalized assignment condition, patients with high levels of distress receive an emotional distress-tailored intervention, patients with pain-related interference receive an exposure/extinction-tailored treatment intervention and patients who adapt relatively well to the pain receive a low-level smartphone-based activity diary intervention. In the control arm, patients receive one of the two non-matching interventions. Effect sizes will be calculated for change in core pain outcome domains (pain intensity, physical and emotional functioning, stress experience, participant ratings of improvement and satisfaction) after intervention and at follow-up. Feasibility and safety outcomes will assess rates of recruitment, retention, adherence and adverse events. Additional data on neurobiological and psychological characteristics of the patients are collected to improve treatment allocation in future studies.

**Conclusion:**

Although the call for personalized treatment approaches is widely discussed, randomized controlled trials are lacking. As the personalization of treatment approaches is challenging, both allocation and intervention need to be dynamically coordinated. This study will test the feasibility and safety of a novel study design in order to provide a methodological framework for future multicentre RCTs for personalized pain psychotherapy.

**Trial registration:**

German Clinical Trials Register, DRKS00022792 (https://www.drks.de). Prospectively registered on 04/06/2021.

**Supplementary Information:**

The online version contains supplementary material available at 10.1186/s40814-022-01199-6.

## Introduction

### Background

As the leading symptom of a wide variety of musculoskeletal disorders, chronic pain is one of the most serious health problems worldwide [1] with enormous consequences on psychological as well as physical health [2, 3]. It is estimated that more than 20% of the world’s adult population suffer from chronic pain and every 10th person is diagnosed with chronic pain every year [4, 5]. While initial causes of pain can often be adequately treated (e.g. surgery, joint replacement, anti-inflammatory drugs/biologicals), in many cases, the pain persists and becomes chronic. This is especially true for chronic musculoskeletal pain (CMSP) conditions where a specific cause for the pain can no longer be detected [3, 5]. These complex persistent CMSP conditions are manifested by a kaleidoscope of symptoms that are temporally dynamic. Various therapies are available, and a multimodal treatment principle is generally recommended [5]. However, the treatment of CMSP is usually difficult and the treatment outcomes are unsatisfactory [4]. Various randomized controlled trials (RCTs) for the treatment of CMSP have led to negative results despite promising outcomes from preclinical and early clinical studies [4, 6, 7]. Accordingly, the most recent Cochrane review found that multimodal pain treatment achieves only small effects on pain and disability immediately after treatment, which had disappeared by follow-up [4].

There is variability between patients in their response to different pain therapies (even in effective treatments), which can significantly limit overall effects in clinical trials. Often psychobiological mechanisms of pain aetiology and maintenance are not considered [6, 8]. This led to calls for personalized pain therapy with a focus on specific disease-eliciting and disease-maintaining mechanisms and the development of empirically based algorithms that determine the optimal treatment or treatment combinations for individual patients to improve both the clinical care of patients with pain and the success rates of established pain management procedures [6, 9]. A major problem may be related to the fact that patients with comorbid mental disorders such as anxiety and depression and a high burden of psychobiological factors may be even more in need of specialized mechanism-based treatments tailored to their specific multiple needs [6, 10, 11]. Across individual diagnostic categories (e.g. fibromyalgia (FM), osteoarthritis (OA) or chronic non-specific back pain (CBP)), chronic pain may be maintained by similar psychobiological, including comorbid mechanisms leading to the need of cross-diagnostic treatment approaches taking into account relevant core mechanisms [6]. There are several core biological and psychological mechanisms that interact with CMSP in complex ways and can determine the development and maintenance and spread of comorbid psychopathology [12]. Variability of these biological and psychological mechanisms in different clinical presentations of chronic pain appears greater between individual patients than between different underlying diseases, suggesting that mechanistic etiologies of the pain chronicity process and subsequent successful treatment are likely to be at the individual level rather than at the disease level [13].

To implement a personalized treatment approach, however, the characteristics of individual patients or subgroups of patients that show common disease mechanism maintaining their pain, which increase or decrease the response to a particular treatment, need to be identified. Based on previous work, including our own, we can distinguish three subgroups of musculoskeletal pain patients: (1) patients who are characterized by extensive dysfunctional behaviours with high levels of fear of pain, proneness to the rewarding and punishing consequences of pain, (2) patients characterized by high levels of (interpersonal) distress and comorbid depression/anxiety and (3) a group that is not characterized by a specific psychobiological characteristics and comorbidity, commonly termed “adaptive copers” [14]. At this point in time, these mechanistic differentiations are solely based on cluster analyses of questionnaire data; however, we have identified pathomechanisms that may be specific for these subgroups [15, 16]. These include functional brain imaging results [15, 16], as well as evidence for specific mechanisms related to maladaptive aversive learning, memory processes, and reduced capacity for pain-memory extinction including fear of pain and anxiety [12, 17]. Similarly, we previously found that high levels of stress and emotional distress, exposure to psychological trauma and high levels of depression were associated with hyperalgesia to deep and widespread pain and that emotional abuse leads to exacerbated spinal pain summation in chronic pain patients [18].

Further, earlier evidence suggests that this clustering is associated with divergent treatment responses. In a feasibility study [19], we treated a group of CMSP patients with high level of emotional distress with an Emotional Distress Desensitization-tailored treatment approach (EDDT) using eye movement desensitization reprocessing (EMDR), focusing on alterations of distressing experiences [20]. We adapted the trauma EMDR treatment manual to the specific needs of CMSP patients with high level of emotional distress [21]. This emotional distress-tailored treatment induced a significant and clinically meaningful reduction of pain intensity and disability [19, 22]. Significantly, the therapy also led to a normalization of the aforementioned changes in the somatosensory function.

Based on findings on the role of maladaptive aversive learning, memory processes and reduced capacity for pain-memory extinction including fear of pain and anxiety involved in chronic pain, an operant treatment approach based on an increase in healthy behaviours and a decrease in pain behaviours was recently expanded to brain-based extinction retraining. This Pain Extinction and Retraining-tailored treatment approach (PERT) yielded excellent results in CMSP patients in pilot studies and increased effect sizes when specifically provided to patients characterized by high dysfunctionality, fear of pain and anxiety, whereas those with high levels of distress profited less [23].

In addition, we also developed and tested a new pain diary that focuses on pain-free phases and activity rather than pain and disability [17]. With this positive pain diary, we aim to investigate momentary mechanisms, prognostic markers and treatment outcomes in daily life using smartphone- and sensor-based ecological momentary assessment (EMA) [24]. We found significantly lower pain and stress and higher mood ratings at the end of a 4-week trial period when the positive activity diary was implemented [17]. Quality of life was significantly improved as well. Ecological momentary assessments provide unique opportunity for real-world, real-time, interactive, adaptive and personalized administration of interventions based on the dynamics of individuals’ experience and behaviour and their interaction with contextual factors in daily life [25, 26]. Therefore, implementing this new pain diary as an ecological momentary low-level diary intervention for real-time and real-world activity-based attention modulation (EMDI) may be a useful intervention for patients with pain but low levels of comorbidity. This EMDI therefore complements the other two approaches, which are more likely to address patients with high levels of emotional stress or dysfunctional behavioural patterns.

Although all three therapeutic approaches address different core mechanisms and patient subgroups, to our knowledge, there are no approaches to date that have investigated the improvement of efficacy through such precise therapy allocation. Furthermore, there is a lack of validated and cross-disease allocation algorithms that would allow a personalized allocation to the different pain interventions. Against this background, this trial will test the feasibility and safety of a personalized pain psychotherapy allocation with three different treatment modules and explore the initial signals of efficacy and utility of such an approach compared to non-personalized allocation.

### Objectives

The primary objective of this study is to investigate the feasibility and safety of a personalized pain psychotherapy approach with three different treatment modules—EDDT, PERT and EMDI. A secondary objective is the initial estimation of efficacy and utility of such a personalized approach compared to a non-personalized approach on different core pain outcome domains.

## Design

The overarching aim of our personalized pain psychotherapy allocation is to allocate an individual to a therapeutic intervention that fits the best based on the individual characteristics of the patient. In our study, we will focus on the allocation of patients to three well-established and well-validated pain patient clusters whose categorization is based on the widely used West Haven-Yale Multidimensional Pain Inventory (MPI) [27]. Based on this questionnaire, patients will be assigned to one of the three clusters [14]. According to their cluster’s assignment, patients will be allocated “personalized” to the best fitting psychological treatment. In the control arm of this study, patients will be allocated to a treatment that does not match their cluster assignment.

This study is part of the consortium ‘PerPAIN - Improving outcomes in chronic musculoskeletal pain through a personalized medicine approach’ funded by the German Federal Ministry of Research and Education (01EC1904A). This report focuses on the implementation of the pilot study subproject ‘Personalized treatment for chronic musculoskeletal pain: a randomized double-blind controlled trial with multifactorial parallel arm design’. The paper presents the study protocol for the trial, adhering to the Standard Protocol Items: Recommendations for Interventional Trials (SPIRIT) Statement [28], while the results of the trial will be reported in line with the CONSORT 2010 Statement: extension for randomized pilot and feasibility trials [29]. An additional file shows this in more detail (see Additional file 1). All participants must provide written informed consent before inclusion in the study. The study has been approved by the Ethics Research Committee II of the Faculty of Medicine, University of Heidelberg (2020-579N) and will be carried out in compliance with the Helsinki Declaration.

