### Overview

Musculoskeletal pain patients will be offered participation in this study until at least 342 patients have been enrolled in baseline assessment and 105 patients have been included into our randomized controlled proof-of-concept study. All 105 patients enrolled in the study will undergo detailed phenotyping before and after intervention, which, together with the response/non-response data from the RCT, will serve to improve the allocation algorithm for future studies. All patients eligible will be randomly assigned 1:1 to a personalized or non-personalized treatment arm (Fig. 1). Personalization is achieved by a targeted allocation either to a therapy focused on emotional distress, a therapy focused on dysfunctional behaviours and maladaptive learning or allocation to a minimal intervention group where adaptive responses to pain will be registered. After baseline assessments (Fig. 1, T_0_) for relevant pathomechanisms, each patient included in the trial will receive either 12 weekly sessions of cluster-matching therapy (intervention arms)—where patients are allocated personalized (i.e. according to their individual pain mechanism)—or non-cluster-matching therapy (control arms) —where they are allocated non-personalized (i.e. randomly assigned between the other two interventions). After the last session, all procedures included in the baseline assessment will be performed as a posttreatment evaluation (Fig. 1, T_1_). Furthermore, a 3-month follow-up by means of telephone interview and questionnaire package will be implemented for patients taking part in the intervention study (Fig. 1, T_2_). At T_2_, the maintenance of the effects on pain and pain-related impairments will be assessed. In order to guarantee a correct evaluation of our primary outcomes in pain change, we will include an extended psychological assessment (details on outcomes are given below).

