### Randomization and allocation

For the allocation of the participants, a computer-generated list of random numbers will be used. Randomization for the pilot study will be carried out by the Interdisciplinary Center for Clinical Trials (IZKS) Mainz using permuted blocks of variable lengths. The randomization lists will be implemented in the electronic case report form system (eCRF) such that randomization can be performed electronically as new participants are added to the study. After providing informed consent and the acquisition of baseline data, participants will be randomly assigned to experimental intervention (personalized allocation) or control intervention (non-personalized allocation) via this eCRF system. Allocation will be managed by an independent study manager involved neither in sequence generation, assessments or treatment. All processes will be monitored and controlled for correctness by the IZKS Mainz. This process will be started only after the enrolled participants will have completed all baseline assessments and it is time to allocate the intervention. Randomization will be stratified by cluster, so that patients have a 50% chance of being allocated to the treatment matching their cluster, and 50% of being allocated to one of the two interventions (25% chance each) not matching their cluster.

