### Sample size calculation

The study will be performed in an exploratory fashion and is planned as a pilot study to describe the feasibility and safety of personalized treatments for CMSP as a primary outcome, as well as an initial estimation of signals efficacy and utility as secondary outcomes. Even though a formal power calculation is not necessary in a pilot study, we nevertheless performed a power calculation to better estimate the initial signals of efficacy and utility.

For power considerations, we use a mixed-model with repeated measurements (MMRM), a two-sided significance level of 5% and a sample size of 90 patients (→45 per study arm →90 total from a total of 105 patients at an assumed dropout rate of 15%). The MMRM takes into account also the interim measurements for each patient and allows therefore a fuller use of the data than an ANCOVA. The sample size of 105 patients allows to calculate our feasibility measures with a 95% confidence interval width from 11 to 19% (for varying proportion 0.1–0.5) based on a Wald interval for binary measures [40]. Moreover, patients with data with at least one measurement can be used for the primary analysis; therefore, we expect fewer patients not to be usable for the analysis compared to an ANCOVA. Between repeated measurements, a correlation of 0.3 is assumed. Then, the study has a power of 80% to detect a true effect size of *f* = 0.22, a power of 85% for *f* = 0.23 and 90% power for a true effect size of *f* = 0.25. Dropouts will be analysed according to the underlying reasons for dropout and distinction will be made between those dropouts that are preventable by modification of study design and those that are not preventable by study design adaptations.

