Feasibility objectives will be quantified. If appropriate, 95% confidence intervals will be calculated based on the Wilson Score interval for binary measures. We favoured the Wilson Score interval against Wald interval due to their good properties for small numbers of trials, compared to Wei and Hutson [40]. For the analysis of the primary outcome, we will use the complete and pseudonymized data set and follow the intention-to-treat approach which includes all patients in the group they were allocated to by randomization. This approach preserves the allocation of treatment by randomization and it will be as close as possible to the ITT ideal of including all randomized patients. As sensitivity analysis, the analysis will be repeated in the per-protocol (PP) set, excluding patients with major protocol violations. Additional sensitivity analyses will explore the effects of the treatments the patients actually received. The null-hypothesis H0 (no difference occurs in the population means with regard to pain severity at T1 between the experimental intervention and the control intervention) will be tested against H1 (there is a difference in the population means of pain severity differences between the two groups at T1 and T0). Provided that the model assumptions are fulfilled, the null hypothesis will be tested using a (robust) mixed linear regression model at a significance level of 5%. The primary outcome (pain severity at T1, difference to T0) will be analysed using mixed-effects model repeated measurements after 4, 8 and 12 weeks (=T1). The analysis will be adjusted for condition, gender and baseline (T0) pain severity. Compound symmetry will be assumed. Because of the exploratory nature of the study, the observed initial signals of efficacy and utility will be considered more important than the *p*-values. The corresponding *p*-values of these tests will be interpreted purely descriptively. We will compute effect sizes and interpret them together with the respective 95% confidence intervals. Regarding secondary endpoints, exploratory data analysis will be performed using appropriate analytical methods depending on the respective parameter. Details of the statistical analyses will be fixed in a statistical analysis plan developed by the statistics department of IZKS Mainz prior to database closure. The safety analysis includes calculation and comparison of frequencies and rates of adverse events. Furthermore, statistical methods are used to assess the quality of data and the homogeneity of intervention groups. All analyses will consider gender aspects. Prior to all analyses, we will pre-specify a statistical analysis plan.

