
To more closely assess the ecological validity of our design in a naturalistic setting, a second analysis will be carried out where 1/3 of matched patients are randomly sampled and statistically reallocated to the non-matching arms. This is to allow a comparison between personalized treatment and truly random assignment (rather than matched vs non-matched), which may more closely mirror the ultimate implementation of personalization methods in clinical services or during a confirmatory multi-centre RCT.

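### The main effect size compares matched with mismatched allocation; the effect against cluster-blind allocation is about two thirds of it, and the planned re-analysis does not recover that figure

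*Protocol article*

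**What the plan says.** The secondary objective is an "initial estimation of efficacy and utility of such a personalized approach compared to a non-personalized approach" (Protocol article, Objectives). The control arm is described consistently. Under Design, control "patients will be allocated to a treatment that does not match their cluster assignment". Under Overview, control patients receive non-matching therapy, "where they are allocated non-personalized (i.e. randomly assigned between the other two interventions". Under Randomization and allocation, each patient has a 50% chance of the matching module and "50% of being allocated to one of the two interventions (25% chance each) not matching their cluster".

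Sample size calculation uses "a two-sided significance level of 5% and a sample size of 90 patients", a repeated-measures mixed model and a correlation of 0.3. It then states: "Then, the study has a power of 80% to detect a true effect size of" f = 0.22, with 85% power for f = 0.23 and 90% for f = 0.25. Statistical analyses fits the model to weeks 4, 8 and 12 and places effect sizes above p-values: "We will compute effect sizes and interpret them together with the respective 95% confidence intervals".

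The last paragraph of Statistical analyses adds a second analysis, in which one third of matched patients are drawn at random and counted with the non-matching arms. Its stated purpose is a "comparison between personalized treatment and truly random assignment (rather than matched vs non-matched"), which the authors think may be nearer to routine services or to a confirmatory multi-centre trial.

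**The concern.** Allocation that ignores the cluster would still give some patients the fitting module by chance. This control arm uses the cluster to withhold it from every patient. Two questions are therefore in play: matching versus mismatching, and matching versus not using the cluster at all. The main effect size answers the first. The second is the one that the protocol itself links to clinical use, and any benefit of matching is smaller there.

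The pilot is meant to prepare a larger trial (Treatment personalization), and effect sizes are its preferred currency. Neither the Objectives, the power paragraph nor the main model says which of the two questions its figures answer. The protocol also does not say which estimate should be carried forward. The one analysis aimed at the second question should deliver the right quantity, and as written it does not.

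**Working it through.** **Inputs.** Allocation within cluster is 50% matched and 25% to each other module (Randomization and allocation). N = 90, two-sided 5%, correlation 0.3, and f = 0.22 / 0.23 / 0.25 for 80 / 85 / 90% power (Sample size calculation). There are three post-baseline visits (Statistical analyses). One input is an assumption: cluster-blind allocation gives each of the three modules with probability 1/3.

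**1. The plan's own figures.** Between-group F test with repeated measures: λ = f² × N × m / (1 + (m − 1)ρ), df 1 and 88, m = 3, ρ = 0.3. The multiplier is 90 × 3 / 1.6 = 168.75.

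| f | λ | power, recomputed | power, stated |
|---|---|---|---|
| 0.22 | 8.17 | 80.7% | 80% |
| 0.23 | 8.93 | 84.0% | 85% |
| 0.25 | 10.55 | 89.5% | 90% |

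The stated powers reproduce to about one point for the pilot's own two arms.

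**2. Matched versus cluster-blind.** Within a cluster, let M be the mean under the matched module and U the equally weighted mean under the two others. A control with a share p matched by chance has mean pM + (1 − p)U, so

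M − [pM + (1 − p)U] = (1 − p)(M − U).

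At p = 1/3 this is 2/3 of the matched-minus-mismatched difference, so the main contrast is 1.5 times as large. The ratio 1/(1 − p) is 1.25 at p = 0.20, 1.33 at p = 0.25 and 1.67 at p = 0.40. These factors are for raw differences. On a standardized scale, mixing adds a little variance to the control arm: at d = 2f = 0.44 its variance is 1 + (1/3)(2/3)(0.44²) = 1.043, and the factor becomes about 1.52.

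**3. What the planned reallocation estimates.** With 105 patients randomized 1:1, there are about 52.5 matched and 52.5 control patients. Moving 52.5 / 3 = 17.5 gives a control of 70, of whom 17.5 / 70 = 25% are matched. The expected contrast is then 0.75(M − U), which is 0.75 / 0.667 = 1.125 times the equal-chance target. A 1/3 share requires x / (52.5 + x) = 1/3, so x = 26.25, which is half of the matched patients.

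**4. Consequence if the main effect were used for sizing.** Suppose the matched-versus-mismatched effect is f = 0.22 and a later trial has a cluster-blind control. The effect there is 0.22 × 2/3 = 0.147. On the plan's model:

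- With 90 patients, λ = 0.147² × 168.75 = 3.63 (unrounded f) and power is 47%. Reaching 80% needs 198 patients in total.
- At f = 0.25 and 90% power, the total rises from 92 to 204, and 92 patients would have 58% power.
- Sizing on the reallocation estimate (0.75 × 0.22 = 0.165) gives 156 patients and about 70% power.

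A two-sample check using the SD of the mean of three visits, √(1.6/3), gives 44 versus 98 per arm and again 47% power.

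**The case against.** The protocol defines its term. Overview says that non-personalized means random between the two other modules, and every other description of the arms agrees. A reader might infer that the objective contradicts the control arm; it does not. The main estimate targets the defined contrast without bias, and a maximal contrast is a legitimate choice for a proof-of-concept study.

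A reader might also conclude that the power figures are inflated. They are not. They are detectable effects for the pilot's own comparison and they reproduce. Two thirds of f = 0.22 is not a corrected version of that figure; it is what the same underlying benefit would look like against a different control.

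A third tempting inference is that the planned trial will be undersized. No section fixes that trial's control arm or ties its size to the main effect, and the protocol says only that random assignment may be the closer model. The shortfall is therefore conditional.

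Finally, the authors recognise the distinction and plan an analysis for it, and efficacy is secondary and exploratory. All of this stands. It does not remove two points: the distinction is missing where the main effect and power are presented, and the analysis meant to bridge it misses its target.

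**Conclusion.** The concern holds in a limited form. The main effect size and the power statement describe cluster-matched versus cluster-mismatched allocation and are correct for it. The raw effect against cluster-blind allocation is 2/3 as large under equal chance over three modules, and (1 − p) times as large in general. No analysis in the protocol delivers that figure as written, because the reallocation yields 0.75 of the contrast. The possible downstream cost, about 47% power instead of 80% at f = 0.22, arises only if a later trial both uses a cluster-blind control and is sized on the main effect. The 2/3 rule also assumes that a module's outcome does not depend on the overall allocation mix, which is worth stating because PERT is delivered in groups. Given the exploratory, secondary status of efficacy, this should be corrected but does not threaten the pilot's primary aims.

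**What to change.** Keep the arms, the randomization and the main model.

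1. In Objectives, Sample size calculation and Statistical analyses, call the contrast *cluster-matched versus cluster-mismatched allocation*, and say that the power figures refer to it.
2. Replace the random reallocation with a direct estimate: 2/3 of the cluster-stratified matched-minus-mismatched difference, with the two mismatched modules weighted equally within cluster and the 95% confidence limits multiplied by 2/3. State the equal-chance assumption. The p-value is unchanged, and the result does not depend on a random draw of patients.
3. Name this as the estimate for conclusions about cluster-blind allocation and for planning any trial with such a control. If another chance share is foreseen, use 1 − p instead of 2/3.

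The cost is wording and one rescaled estimate, with no new patients or data. The downside is that the effect reported for the cluster-blind question is one third smaller than the main one.
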